**Methods and analysis:**

The study is a real-world evaluation with observational data collection. We will recruit 450 study participants from four NHS specialist WMS who will choose either standard NHS WMS or the digital pathway Gro Health W8Buddy. Participants are being given the option to choose their pathway to generate real-world evidence. We will measure and analyse health outcomes including weight loss, time taken to be treated and cost-effectiveness, at 18 months and follow up at 24 months for later analysis (outside of this core funding). We will gather experiential data from patients and healthcare professionals through surveys, observation and interviews.

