### Sample size calculation

We will collect weight data at baseline and a minimum of three occasions during the study, for both pathways. Powering the study to show that the digital pathway is non-inferior to the standard of care pathway, with a difference less than 4 kg, at 90% power and a two-sided 5% level, gives a sample size of approximately 180 participants. Further assuming a correlation between the repeated weight measurements in the range 0.2–0.5, which previously collected data suggests is reasonable,^28^ based on a longitudinal mixed model/repeated measures Analysis of covariance (ANCOVA) gives a total sample size of 360. Conservatively assuming 20% loss during follow-up, the target sample size is 450.

Given the current widespread use of the digital (W8Buddy) intervention at the lead centre (UHCW), the control (standard of care; SC) intervention at this site will be different from that offered at the other sites. For this reason, we plan to characterise the control intervention at UHCW as a ‘hybrid’ digital intervention. We will aim to recruit sufficient participants (ie, 360) at the three other sites (UHB, LLT, HDUHB) to fully power the study for the planned comparison between the digital and standard of care groups. Additionally, we will collect data from the ‘hybrid’ digital intervention at UHCW to augment and further refine the primary analysis.

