**Figure 1 F1:**
[figure not shown]
Participant flow chart. The flow chart describes where participants will be providing data in both the digital and standard of care arms. PI, principal investigator.

Eligible participants will be able to choose how they receive their WMS—either in the standard NHS delivery, or via fully digital platform Gro Health W8Buddy. Site-specific standard of care pathways will be delivered by the usual healthcare professionals, employed by each NHS site. The digital pathway will be delivered by healthcare professionals employed by DDM (providers of Gro Health W8Buddy). We aim to recruit a total of 450 participants across both arms from September 2025 to February 2026.

Those who satisfy the study inclusion criteria will be contacted by the research team via telephone. Brief information about the study will be provided to potential participants, including a link to a website with information about the study. This website will be password protected as only eligible participants will be able to view it. Digital information sheets and consent forms will be hosted on the website.

If a patient is unable to access the website (therefore, unable to complete electronic consent), the local site research nurse will invite them to the hospital. They will show the participant the research website and help them with electronic consent. Later, the research nurse will print out the consent form (signed copy) only for the patient if they do not have access to email.

Electronic consent for data collection, with an option to consent for ongoing data collection, will be obtained. Following informed consent, participants will be able to choose the digital or standard care pathway via the website. A copy of the signed consent form will be sent to the participants, local research team and site principal investigator (PI).

To support data collection in the standard care pathway, participants will be offered a £10 voucher for each completed survey at months 0, 6, 12, 18 and 24; vouchers will not be provided for sign up only, surveys must be completed by participants.

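### The 360 participants needed after loss to follow-up are reused as the three-site recruitment target, so the digital versus standard-care comparison falls short of its stated 90% power

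*Protocol article*

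**What the plan says.** All the sample size figures are in the Protocol article, Sample size calculation.

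- The aim and margin: "Powering the study to show that the digital pathway is non-inferior to the standard of care pathway, with a difference less than 4 kg".
- The first step: "at 90% power and a two-sided 5% level, gives a sample size of approximately 180 participants".
- After allowing for repeated weights, the calculation "gives a total sample size of 360".
- The loss allowance: "Conservatively assuming 20% loss during follow-up, the target sample size is 450".
- The next paragraph labels the control at UHCW a hybrid digital intervention and turns to the remaining sites: "We will aim to recruit sufficient participants (ie, 360) at the three other sites (UHB, LLT, HDUHB) to fully power the study". It adds that data from the UHCW hybrid intervention will be collected as well, to augment and refine the primary analysis.

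Two other places fix the total. The abstract says: "We will recruit 450 study participants from four NHS specialist WMS". Screening, recruitment and consent says: "We aim to recruit a total of 450 participants across both arms from September 2025 to February 2026". Primary and secondary outcome analysis describes the comparisons with the hybrid intervention as secondary and unpowered.

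**The concern.** The two paragraphs of the sample size section give 360 two different meanings. In the first it is what must be left after 20% loss. In the second it is what will be recruited at the three sites that carry the powered comparison. The total stays at 450 for four sites, so no loss allowance remains at the three sites: the 90 places that were that allowance are also the only places left for UHCW.

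At stake is the stated power of the study's one powered comparison. If a truly equivalent digital pathway fails to show non-inferiority, readers will judge that result against a claimed 10% type II error that the plan's own figures do not support. The protocol itself treats attrition as likely. Its background reports retention below 55% in conventional services, and its risk table lists high dropout in standard care.

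**Working it through.** **Inputs, all from the protocol article unless marked**

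- Margin 4 kg, 90% power, two-sided 5%: z(0.975) = 1.960, z(0.90) = 1.282, sum 3.2415.
- Number giving 90% power: 360 in total.
- Loss: 20%. Total recruitment over four sites: 450. Recruitment at UHB, LLT and HDUHBT: 360.
- Assumed: 1:1 allocation (participants choose their pathway, so no ratio is fixed). The SD is not stated in the article, but the main result does not need it.

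**1. Reproduce the plan's figure.** 360/(1 − 0.20) = 450, an exact match. Multiplying instead (360 × 1.2) would give 432. So 360 is the number required after loss. The earlier steps to 180 and then 360 cannot be reproduced without the SD, so 360 for 90% is taken as given.

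**2. Places left for UHCW.** 450 − 360 = 90. This is by subtraction; no passage states it.

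**3. Retained at the three sites.** 360 × 0.8 = 288.

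**4. Power on a completer basis.** With the margin, SD and allocation unchanged, power depends only on the ratio of analysed numbers:

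Power = Φ(3.2415 × √(288/360) − 1.960) = Φ(0.939) = 0.826.

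Type II error is therefore 17.4% against the stated 10%. As a cross-check, an SD of 11.7 kg makes 180 per arm give 90% power at 4 kg; with that SD, 144 per arm again gives 82.6%. Reading the level as one-sided 5% gives 83.5%.

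**5. Sensitivity of the completer figure**

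| Condition | Analysed at three sites | Power |
|---|---|---|
| 10% loss, 1:1 | 324 | 86.8% |
| 20% loss, 1:1 | 288 | 82.6% |
| 30% loss, 1:1 | 252 | 77.4% |
| 20% loss, 60:40 | 288 | 81.1% |
| 20% loss, 70:30 | 288 | 75.7% |

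**6. If partial follow-up counts.** Assume a linear-slope mixed model with separate baseline means by arm, compound symmetry, weights at 0, 6, 12 and 18 months, and correlations of 0.2 and 0.5 (the ends of the plan's range). Losing 20% then leaves a fraction e of the full-data information on the slope difference, between about 0.839 and 0.894 depending on when loss occurs. Power = Φ(3.2415 × √e − 1.960) is then about 84% to 87%. If the model instead constrains the arms to a common baseline, participants lost straight after baseline add nothing and the figure returns to 82.6%.

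**7. If UHCW's fully digital participants are pooled into the digital arm.** 90 × 0.8 = 72 retained at UHCW. If 25, 50, 75 or 100% of them are fully digital, the digital arm is 162, 180, 198 or 216 against 144 in standard care. Completer power is 84.7, 86.3, 87.7 or 88.8%.

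**8. The other reading of 360.** If 360 at the three sites was meant as completers, 360/0.8 = 450 must be enrolled there. That leaves 450 − 450 = 0 places for UHCW, although the article lists it as a recruiting site.

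**The case against.** The strongest reply is that 83% is not the power of the planned analysis. The primary analysis is a longitudinal mixed model of rates of weight change, so people lost during follow-up still contribute the weights they gave. Only the control at UHCW is labelled hybrid; participants there may also choose the fully digital pathway, and the protocol says UHCW data will augment the primary analysis. Both points stand, and for them 83% is a completer figure that more data would raise. Neither restores 90%, taken singly: steps 6 and 7 stay below it. The plan also applied its full 20% allowance to this same longitudinal model in the first paragraph, so it cannot treat that allowance as unnecessary in the second. And it says the three sites alone fully power the comparison, with UHCW additional.

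It is also fair that the 360 cannot be verified without an SD, that allocation is by choice, and that the 90 at UHCW is inferred. These limit the certainty of the power figure. They do not remove the double use of 360, which is plain from the text.

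Three stronger readings are tempting and are not supported:

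- That the trial's power simply is 83%, so that equivalence would be missed almost twice as often as planned. The ratio 17.4/10 = 1.74 holds only on a completer basis. At 84% to 87% power it is about 1.3 to 1.6.
- That the shortfall undermines the result itself. A smaller sample does not by itself bias the estimate, move the margin or raise the rate of false non-inferiority claims.
- That 90% can be recovered by moving places between sites at no extra cost in participants. With all 450 at three sites, nobody is left for the hybrid comparison that the analysis section plans.

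**Conclusion.** The inconsistency is real and rests on the plan's own figures. The powered comparison has no loss allowance, and the stated 90% does not hold at the stated 20% loss. The size is conditional: about 83% on a completer basis at the three sites, given 360 for 90% and 1:1 allocation; somewhat higher, but still short of 90%, if partial follow-up or UHCW's fully digital participants are counted; lower if pathway choice is unbalanced. The double use of 360 is certain; the exact power is not. The point deserves correction because full power is claimed explicitly for the study's only powered comparison.

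**What to change.** In Sample size calculation, remove the claim that 360 recruited at the three sites fully powers the study at 90%, and restate the figure, for example:

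> 360 recruited at UHB, LLT and HDUHBT, of whom about 288 are expected to have an 18-month weight, giving about 83% power for the 4 kg margin on a completer basis with equal allocation.

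If the team prefers a figure for the mixed model or with UHCW's fully digital participants included, it should state the assumptions behind it. This option changes wording only; the cost is a less favourable stated power.

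The alternative is to keep 90%, which needs 450 recruited at the three sites with UHCW counted separately. That exceeds the present total: 450 + 90 = 540 if UHCW still contributes 90. It is a recruitment decision and not an edit.

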### Screening, recruitment and consent

Potential participants will be identified by research nurses once they have been referred (or self-referred) to the local Tier 3 WMS. Participants will be screened electronically against pre-specified criteria (figure 1).

**Figure 1 F1:**
[figure not shown]
Participant flow chart. The flow chart describes where participants will be providing data in both the digital and standard of care arms. PI, principal investigator.

Eligible participants will be able to choose how they receive their WMS—either in the standard NHS delivery, or via fully digital platform Gro Health W8Buddy. Site-specific standard of care pathways will be delivered by the usual healthcare professionals, employed by each NHS site. The digital pathway will be delivered by healthcare professionals employed by DDM (providers of Gro Health W8Buddy). We aim to recruit a total of 450 participants across both arms from September 2025 to February 2026.

Those who satisfy the study inclusion criteria will be contacted by the research team via telephone. Brief information about the study will be provided to potential participants, including a link to a website with information about the study. This website will be password protected as only eligible participants will be able to view it. Digital information sheets and consent forms will be hosted on the website.

If a patient is unable to access the website (therefore, unable to complete electronic consent), the local site research nurse will invite them to the hospital. They will show the participant the research website and help them with electronic consent. Later, the research nurse will print out the consent form (signed copy) only for the patient if they do not have access to email.

Electronic consent for data collection, with an option to consent for ongoing data collection, will be obtained. Following informed consent, participants will be able to choose the digital or standard care pathway via the website. A copy of the signed consent form will be sent to the participants, local research team and site principal investigator (PI).

To support data collection in the standard care pathway, participants will be offered a £10 voucher for each completed survey at months 0, 6, 12, 18 and 24; vouchers will not be provided for sign up only, surveys must be completed by participants.

### Intervention Gro Health W8Buddy

Gro Health W8Buddy is a virtual specialist WMS pathway. It is accessed through a digital behavioural change platform called the Gro Health app (see, figure 2). Participants on the W8Buddy digital arm will receive 52 weeks of support from healthcare professionals employed by DDM. At week 52, each participant on the digital pathway will be assessed and the following options offered: discharge to primary care, onward referral to local tier 4 if interested in surgery, onward referral for local tier 3 MDT discussion, extension of digital pathway by 6 months, referral to local tier 2 WMS.

**Figure 2 F2:**
[figure not shown]
Gro Health W8Buddy platform and app—description and visual representation of the W8Buddy platform in an app format.

### Standard care

Participants in the standard care arm will receive the tier 3 WMS that is delivered by their local NHS trust. All four NHS trusts included in the research have differences in their tier 3 service, which will be explored in detail as part of the study. The differences range from the amount of input from healthcare professionals (psychologist, dietitian, physician), modality of sessions (1–1 or group sessions) and frequency. Post study care for participants in standard care will be delivered in accordance with their NHS trust policies for tier 3 wt management. As discussed previously, the W8Buddy intervention is included in the standard of care at the lead centre (UHCW). It is used as a digital support tool only (no access to clinicians via W8Buddy), enhancing the usual face-to-face care, and as such, differs from entirely remote digital pathway. For this reason, the model of delivery of care is hybrid at UHCW (refer to table 1 for further detail).

**Table 1 T1:** Standard of care

NHS site	Standard of care	Weight management medication offered in current tier 3 service*
UHCW	Hybrid standard of care with digital W8Buddy input and in person MDT support. Mixture of one-to-one and group sessions delivered by dietitians, psychologists and consultant endocrinologists.	No
UHB	Mixture of group sessions and one-to-one appointments delivered by dietitians, psychologists and consultant endocrinologists following a face-to-face introductory group session.	No
LLT	Mixture of face-to-face and group sessions delivered by psychologists, dietitians and consultant endocrinologists.	No
HDUHBT	Mixture of face-to-face and group sessions delivered by psychologists and dietitians. After completion, they are seen by a consultant.	Yes

*Please note this information is accurate at time of publication.

HDUHBT, Hywel Dda University Health Board Trust; LLT, London Luton Trust; MDT, multidisciplinary team; UHB, University Hospitals Birmingham; UHCW, University Hospital Coventry & Warwickshire.

### Assessment and management of risk

Risks relate to data management/reporting across four sites and management of the digital pathway delivered by DDM. The latter is assured by DDM. Table 2 lists these. Further information on data management and flow can be found in online supplemental table 2, adverse events (online supplemental table 2) and online supplemental figure 1.

10.1136/bmjopen-2025-109111.supp5Supplementary data

10.1136/bmjopen-2025-109111.supp1Supplementary data

**Table 2 T2:** Assessment and management of risk

Data reporting	Not reporting data by participants, mitigated by regular support via the app or contact from the research team if not completing surveys.
Data protection	As with any online service, proper data handling is assured by high security data storage in line with NHS Digital policies. Data from NHS sites transferred to analytical partner using secure pathways.
Delivery	The site research team will oversee all participants, including those accessing digital pathway. The first contact for any queries for participants on the digital pathway will be the digital provider, and if the query is not resolved, the research site team will be contacted. The project will be managed by PH and AG via weekly WP meetings between sites and project manager, with monthly oversight by each site PI. Three-monthly meetings of the PPIE group will ensure ongoing input from patients. Annual project steering committee meetings will review risk registers.
Imbalanced recruitment	More patients opting for digital rather than standard of care pathway (or vice-versa), mitigated by over-recruiting standard of care (or digital) patients and adjusting as per analysis plan using propensity-weighted approach, purposive sampling and ongoing monitoring of recruitment, communication to sites, telephone and offline packs as another option for those choosing digital pathway.
Engagement with the digital pathway	Low engagement from high-risk/target groups resulting in lower enrolments and participation from those most in need of the service. Mitigated by patient-friendly resources, onboarding support and a research nurse at each site to act as a point of call.
Patient safety	Without face-to-face contact, healthcare professionals may miss important physical signs and symptoms that might indicate a health concern for study participants. Participants might also misunderstand or misuse instructions regarding their medication, increasing the risk of side effects or adverse events. This is mitigated through symptom tracking, face-to-face videoconferencing/virtual calls, identifying signs of body language and recording sessions for audit to ensure ongoing patient safety. Digital phenotyping of patients occurs in real-time, and any thresholds of anxiety or depression are noted in the clinical dashboard and the clinical team are notified. Omni-directional communication through the platform allows clinicians to engage directly with patients and vice versa with up-to-date, real-time data. Patient expectations are managed by informing the patient if their coach is offline and encouraging them to seek emergency medical assistance if at risk.
Medication safety on the digital pathway	Prescribing medication remotely requires a comprehensive understanding of the patient’s current health status, medications and lifestyle, which can be challenging to obtain in a virtual environment. There is also the risk of potential drug interactions that might be overlooked without a detailed in-person evaluation. This is mitigated through patient completion of psychological assessments, medication eligibility assessment and approval for medication from the multidisciplinary team (MDT)) providing the patient’s care. Regular reviews ensure medication is not mismanaged and appropriate for the patient. Patient is provided with videos and resources on how to inject.
Psychological safety on digital pathway	Weight management is closely tied to self-esteem and body image, which can be negatively impacted if the focus is solely on weight loss. Additionally, the digital nature of virtual services can exacerbate feelings of isolation and lack of support. This is mitigated through support from a psychotherapist/psychologist throughout the programme, access to private/group coaching for on-demand support, and artificial intelligence algorithms that provide digital phenotype measurements for a patient’s likelihood of anxiety, stress and depression based on conversations/engagements in the community.
Eating disorders	Weight loss can trigger or exacerbate eating disorders. For individuals with a history of eating disorders, weight loss medications could potentially be misused in a harmful way. This is mitigated through patient completion of psychological assessments, medication eligibility assessment and approval for medication from the MDT team providing the patient’s care. On the digital pathway, regular reviews with a pharmacist and psychologist ensure medication is not mismanaged and appropriate for the patient. Signposting and referral back to the GP will be provided to any patients who display signs of disordered eating. On the standard of care pathway, local protocols will be followed.
Engagement with the standard of care pathway	High drop out from the standard of care pathway: there is a high drop out from the standard of care service in tier 3 Weight Management, resulting in high loss to follow-up. This will be mitigated by having a dedicated research nurse who will contact patients to ensure they complete all data collection in a timely fashion. Additionally, participants in the standard of care will receive vouchers to compensate them for the additional surveys they will be asked to do.

GP, general practitioner; PI, principal investigator; PPIE, Patient and Public Involvement and Engagement; WP, work packages.

### Outcomes

The primary outcome is changes in body weight after 18 months of using either (1) a fully digital weight management programme (remote digital pathway Gro Health W8Buddy) or (2) site-specific delivered weight management programmes incorporating face-to-face and/or virtual group sessions (standard care).

Secondary outcomes are metabolic markers (HBA1c, lipids), blood pressure, waist circumference and health-related QoL (EQ-5D-5L).^28^

